### Outcomes

Outcome measures and predictors of outcome are listed in table 2.

**Table 2 T2:** Outcome measures, predictors of outcome and instrumentation

	Instruments	T0	T1	T2	T3
**Primary outcome parameters**					

Fatigue severity	Checklist Individual Strength (CIS subscale fatigue) [19]	X	X	X	X

Physical Functioning	Child Health Questionnaire (CHQ-CF87 subscale physical functioning) [20]	X	X	X	X

School presence	Last two weeks school presence expressed in attended hours/obliged hours * 100%[3]	X	X	X	X

**Secondary outcome parameters**					

Self rated improvement	short questionnaire consisting of 3 items [3]	X	X	X	X

**Possible patient's predictors of treatment outcome**					

Depression score	Child Depression Inventory (CDI) [21,22]	X			

Anxiety score	Spielberger State-Trait Anxiety Inventory for Children, STAIC [23,24]	X			

Somatisation score	Children's Somatisation Inventory (CSI) [25,26]	X			

Physical activity	Actometer and Self-observation list daily functioning [27,28]	X	X	X	

Self-efficacy	Self Efficacy Scale-28[2]	X			

Perceptions of parental rearing behaviours	EMBU-A [29]	X			

**Possible parental predictors of treatment outcome**					

Fatigue severity	Checklist Individual Strength (CIS subscale fatigue) [19]	X			

Psychological distress	Symptom Checklist (SCL-90) [30,31]	X			

Focussing on bodily symptoms	subscale private body consciousness of the Body Consciousness Scale [32,33]	X			

Perceptions of rearing behaviours	EMBU-P [34]	X			

Causal attributions	CAL [19]	X			

The primary outcome measures are: (1) Fatigue as measured by the subscale *fatigue severity *(8 items, 7-points Likert Scale) of the Checklist Individual Strength-20 [19] with a severity range from 8-56. The questionnaire has good reliability and discriminative validity. (2) Physical functioning as measured by the subscale *physical functioning *(9 items) of the validated Dutch translation of the Child Health Questionnaire (CHQ-CF87) (0-100%) [20], and (3) School presence (expressed in attended hours/obliged hours * 100%) as assessed in prior intervention studies in adolescents with CFS[3]. Secondary outcome measure is self-rated improvement, measured using a short questionnaire consisting of 4 items as assessed in prior intervention studies in adolescents with CFS [3]: patients indicate whether they have completely recovered, feel much better, have the same complaints of have become worse compared with the previous measurement.

Outcome measures will be obtained at the UMCU at the start of the study period (T0), after the intervention 6 months later (T1) and after 6 months follow-up (T2). For those adolescents primarily allocated to usual care who will start with FITNET at T1 - in case of no recovery - there will be an extra follow-up moment after 12 months (T3), *see figure *1.

At the first measurements (T0) demographic data and the following predictors of response to treatment and measures of processes of change will be obtained by the primary investigator (SN) both for adolescent and parent(s) *(see table *2*)*. Possible predictors of response to treatment in adolescents are: (a) Depression score (validated Dutch translation of the Child Depression Inventory, CDI) [21,22], (b) Anxiety (Dutch translation of the Spielberger State-Trait Anxiety Inventory for Children, STAIC) [23,24], (c) Number and severity of other somatic symptoms measured by a validated Dutch translation of the Children's Somatisation Inventory (CSI) [25,26], (d) Physical performance as measured with the actometer. This is a motion-sensing device worn at the ankle that registers and quantifies physical activity. The actometer is worn day and night during a period of twelve consecutive days [27]. During the same days patients rate fatigue, pain and activity levels on a prescheduled diary four times daily on a scale of 0 (not at all) to 4 (very much). Daily registration of hours being at school is registered as well. The psychometric qualities are good [28], (e) Self-efficacy (Self Efficacy Scale-28) [2], (f) Perceptions of parental rearing behaviours (the adolescent version of the Egna Minnen Beträffende Uppfostran, EMBU-A) [29].

Possible parental predictors of response to treatment are: (a) Parental fatigue (Checklist Individual Strength-20) [19], (b) Parental psychological distress measured by the Symptom Checklist (SCL-90) [30,31], (c) Parental focussing on bodily symptoms by the subscale private body consciousness of the Body Consciousness Scale [32,33], (d) EMBU-P, the parental version of the Egna Minnen Beträffende Uppfostran [34], (e) parental causal attributions to the origin of CFS (Causal Attribution List, CAL) [19,28].

Finally, the patients and parent(s) treated with FITNET (including the drop-outs) will be interviewed (responsive evaluation) about their experiences with the FITNET intervention. The interviews are semi-structured, with open questions guided by a topic list (10 point scale, questionnaire especially developed for this study). Different aspects of this web-based programme will be evaluated: text, lay-out, feedback by the therapist, scheduling of modules, technical experience, etc.

### Adverse events

The delivery of CBT to adolescents and adults is considered safe.

All adverse events reported spontaneously by the participants or observed by the therapists will be recorded. All adverse events will be followed until they have aborted, or until a stable situation has been reached.

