### Interventions

#### Usual care

The patients in the control group will receive the usual care available in the region where the patient lives. The available usual care for adolescents with CFS in the Netherlands includes: individual/group based rehabilitation programs, psychological support including CBT face-to-face, graded exercise therapy by a physiotherapist, etc. All care received will be monitored during the study.

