#### Web-based Cognitive Behavioural Therapy (FITNET)

FITNET is a web-based cognitive-behavioural treatment accessible to patients and both parents, based on the existing face-to-face CBT protocol for adolescents developed by the ECCF [3,17]. Trained cognitive behavioural psychotherapists from the ECCF will support the patients by e-consults. There will be no face-to-face contact between the therapists and patients at all.

The web portal is designed by the UMCU in collaboration with the ECCF, and has been developed in cooperation with adolescents with CFS who critically appraised text, lay-out and structure. Two authors of children books ([name]) revised the textual content on readability for adolescents. All therapists receive a special half a day training in the application of written language for this target group.

The programme consists of a psycho-educational and a CBT section. The psycho-educational section will be readily available, after receiving log in codes. The CBT section consists of 21 interactive modules (*see appendix 1*), accessible upon activation by the therapist. The web-based therapy comprises about 20 internet-sessions over 6 months. Meanwhile, the parents will follow a parallel program. All users will have a unique username and password, ensuring private communication with the therapist. Both parents and adolescents will have a regular e-consult (email contact) with the therapist, wherein results so far are discussed and new assignments can be given. The therapist will reply on a fixed weekday. The patient will have the ability to send an emergency email, on which a prompt reply will be made. For emergency situations, telephone contact details are available for the patient.

The FITNET treatment programme is implemented in a portal with a lay-out especially designed for adolescents, combining different applications such as: e-consult, personal diaries, questionnaires, psycho-education, all treatment steps and the possibility to review previous communications and assignments. Patient data and emails will be encrypted and securely stored on the UMCU mainframes to guarantee privacy and confidentiality. The treatment protocol is described in more detail in the appendix.

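### Adverse events are recorded only if volunteered or seen by therapists, whom the trial supplies only to FITNET up to T1, so recorded events are not comparable between arms

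*Protocol article*

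**What the plan says.** The Adverse events section of the protocol article gives two routes by which an event enters the record: "All adverse events reported spontaneously by the participants or observed by the therapists will be recorded". It adds that events are followed until they end or become stable, and it regards CBT as safe.

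The FITNET section describes the therapists: "Trained cognitive behavioural psychotherapists from the ECCF will support the patients by e-consults". Contact is frequent: "The web-based therapy comprises about 20 internet-sessions over 6 months", and "Both parents and adolescents will have a regular e-consult (email contact) with the therapist", who answers on a set day of the week. There is also an urgent route: "The patient will have the ability to send an emergency email, on which a prompt reply will be made".

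For the other arm, the Usual care section says: "The patients in the control group will receive the usual care available in the region where the patient lives". That care may include psychologists or physiotherapists. The section also says: "All care received will be monitored during the study".

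Study design lets controls enter FITNET only once the first 6 months are over. The Outcomes section schedules assessments for everyone at T0, T1 (6 months) and T2 (6 months later), with T3 added only for controls who start FITNET at T1. Table 2 lists fatigue, physical functioning, school presence and self-rated improvement at these times. It lists no adverse event enquiry.

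**The concern.** Under the stated rule, the chance that an event is recorded depends on how much contact a family has with the trial, and that differs by arm throughout the main comparison period. A FITNET family can mention an event in a routine message, and a therapist can notice one. A control family has to volunteer it to the trial without a comparable channel.

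If more events were recorded under FITNET, a reader could not tell a real excess from closer watching. A real excess could equally be dismissed as closer watching. The participants are adolescents aged 12-18 in a programme that builds up activity without face-to-face contact with the therapist, so a usable account of harms has value. The fault lies in data collection: no later analysis plan can recover events that were never asked about in controls.

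**Working it through.** The document gives no event rate, capture rate or harm hypothesis, so there is no figure to reproduce. The check is a comparison of the relevant sections, followed by an illustration.

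**Sections side by side, T0 to T1**

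| Route to the record | FITNET | Usual care |
|---|---|---|
| Spontaneous report | Yes, with regular e-consults and an emergency email as occasions | Yes, with no comparable channel described |
| Observation by trial therapists | Yes (ECCF psychotherapists) | None described |
| Scheduled outcome assessments | T0, T1 | T0, T1 |
| Adverse event enquiry listed at those assessments | No | No |

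Three further points:

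1. The word therapists could be stretched to cover regional providers. The FITNET section uses it for the ECCF staff, and no duty or channel for regional providers to report to the trial is given.
2. The monitoring promised under Usual care is of care received. It might bring to light events that led to care, but it is not stated as event ascertainment.
3. Controls cannot start FITNET before 6 months, so the difference in contact lasts for the whole main comparison period.

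**Illustration (all rates are assumptions)**

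Let the true risk p be the same in both arms. Let s be the share of events volunteered in either arm, and t the share of the remaining events picked up by therapists, in FITNET only.

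- Recorded in usual care: p × s
- Recorded in FITNET: p × [1 − (1 − s)(1 − t)]
- Apparent relative risk: [1 − (1 − s)(1 − t)] / s, which does not depend on p

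| s | t | FITNET capture | Apparent relative risk |
|---|---|---|---|
| 0.5 | 0.25 | 1 − 0.5 × 0.75 = 0.625 | 1.25 |
| 0.5 | 0.50 | 1 − 0.5 × 0.50 = 0.750 | 1.50 |
| 0.5 | 0.75 | 1 − 0.5 × 0.25 = 0.875 | 1.75 |
| 0.3 | 0.25 | 1 − 0.7 × 0.75 = 0.475 | 1.58 |
| 0.3 | 0.50 | 1 − 0.7 × 0.50 = 0.650 | 2.17 |
| 0.3 | 0.75 | 1 − 0.7 × 0.25 = 0.825 | 2.75 |
| either | 0 | s | 1.00 |

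Example: p = 0.20, s = 0.5 and t = 0.5 give 0.20 × 0.5 = 10% recorded in usual care and 0.20 × 0.75 = 15% in FITNET. With 140 / 2 = 70 per arm, that is 7 against 10.5 expected participants with a recorded event, when the true risks are equal.

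The formula assumes the same s in both arms. More occasions to volunteer would raise s in FITNET and widen the gap. Against that, Study design has FITNET patients agree to forgo further medical examinations and other treatments for fatigue during therapy, which could reduce medical detection in that arm. The likelier direction is over-recording in FITNET relative to usual care, but the text does not settle it.

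**The case against.** The strongest objections are these.

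- **No harm comparison is planned.** The Statistical Analysis section covers an efficacy analysis at 6 months, descriptive 12-month measurements and exploratory predictor analyses. The Adverse events section promises only to record and follow events. This stands. A reader might infer that a planned harm comparison is biased by design, but the document contains no such comparison. The problem attaches to any between-arm reading someone later makes of these records.
- **Symptomatic worsening is already measured alike.** Fatigue, physical functioning, school presence and self-rated change are collected at T1 in both arms with the same instruments. This also stands, so it would be too strong to say that harms at 6 months cannot be compared at all. These measures are listed only as efficacy outcomes, however, and would not identify discrete events such as an injury or a psychiatric crisis.
- **A journal article is condensed.** A T1 enquiry might exist in a fuller protocol. Its absence from Table 2 does not prove otherwise, and the point does not rest on that absence. It rests on the capture rule that the article states, which is unequal as written.
- **The sizes are assumed.** This is true. They show how the mechanism works and are not estimates for this trial.
- **Safety is not simply presumed.** A reader might infer that from the remark that CBT is considered safe, but the next sentences commit to recording and following events.

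**Conclusion.** The point holds in limited form. Following the stated rule makes ascertainment of adverse events depend on arm from T0 to T1, because trial therapists and frequent trial contact exist only under FITNET. Any between-arm summary of recorded events for that period would mix true differences with differences in capture.

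The size is unknown. The range of 1.25 to 2.75 for the apparent relative risk holds only for volunteered capture of 30% to 50%, additional therapist capture of 25% to 75%, and no true difference. The conclusion itself needs no such figures. It assumes only that the therapists named in the rule are the FITNET therapists and that regional providers have no reporting route to the trial; both follow from the text as written.

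The efficacy analysis is unaffected, and so is the comparison of symptomatic worsening at T1.

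**What to change.** - At T1, put the same short set of adverse event questions to every participant in both arms, and name the answers as the source for any between-arm harm summary.
- List spontaneously reported and therapist-observed events separately, by arm, and state that the two arms did not have the same opportunity for capture.
- Tabulate by arm at T1 the proportion who rate themselves as worse, and the change from T0 in fatigue, physical functioning and school presence. These data are already collected.
- Treat harm data at T2 and T3 as descriptive only. Controls may have started FITNET after T1, and T3 exists only for controls who did, so neither time point gives a clean comparison of FITNET with usual care.

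The cost is a few questions at an existing assessment and one extra table. The downside is that more minor events will be recorded. Treatment, eligibility and the efficacy analysis do not change.

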### Statistical Analysis

One-hundred-forty newly diagnosed CFS patients will be included in two years. The data will be analysed on an intention to treat basis. Prognostically important baseline characteristics will be tabulated by treatment modality in order to evaluate success of randomisation. The main efficacy analysis will pertain to the data obtained after a 6 months FITNET or usual care condition. Differences between treatment groups concerning the primary outcome measures will be expressed as relative risks and 95% confidence intervals or as central estimators and variance measures where appropriate. In case of baseline differences in prognosis between groups, treatment effects in primary outcome will additionally be adjusted for these differences using logistic regression for binary outcome data and linear regression for continuous outcome measures. At 12 months follow-up after randomization, a repeated measurement of the primary outcome measures will be undertaken as well as an evaluation of participants' experiences with the FITNET intervention. The latter measurements will have a descriptive nature.

Concerning the predictors of outcome, the study will be merely exploratory because statistical power is not calculated for subgroup analyses. To that end, linear regression analysis will be used with primary continuous outcome measures as dependent variables and interaction terms of putative response predictors and treatment modality as independent variables. Separate analyses will be run for predictors in adolescents and predictors in parents respectively.

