### Power

We estimate that under care as usual the estimated average percentages of school absence, our primary endpoint, at the end of follow-up, will be 40%. Given the efficacy of face to face CBT in adolescence [3] we consider a reduction of school absence of 15% in the e-intervention group to be realistic and highly relevant. In order to statistically detect such a reduction, given a 2 sided-alpha of 0.05 and with 90% power, we will need to allocate 60 patients to each group. In order to accommodate a small anticipated percentage of non-participation we will include 140 diagnosed patients.

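### The plan allows relative risks for three continuous primary outcomes, though no binary endpoint is defined and the sample size fits only a comparison of means; baseline adjustment is left conditional

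*Protocol article*

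**What the plan says.** The Outcomes section and Table 2 of the protocol article define the primary outcomes on numeric scales:

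- Fatigue is a subscale score "with a severity range from 8-56".
- Physical functioning is a Child Health Questionnaire subscale score running from 0 to 100.
- School presence is "Last two weeks school presence expressed in attended hours/obliged hours * 100", a percentage.

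The Power section sizes the trial on "the estimated average percentages of school absence", which is a mean. The Statistical Analysis section, in its paragraph on predictors, itself describes the primary outcomes as continuous.

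That section nevertheless says that between-group differences in the primary outcome measures "will be expressed as relative risks and 95% confidence intervals or as central estimators and variance measures where appropriate". On adjustment it says: "In case of baseline differences in prognosis between groups, treatment effects in primary outcome will additionally be adjusted for these differences", and this is to be done "using logistic regression for binary outcome data and linear regression for continuous outcome measures".

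**The concern.** The effect measure is stated as an either/or, and one branch does not fit the outcomes it is meant for. A relative risk compares two proportions, so using one for fatigue, physical functioning or school presence means first turning the score into success or failure. The article neither names such an endpoint nor says when the relative risk would be the appropriate choice. For three primary outcomes, the scale of the main result therefore stays open in this text, and one of the two scales conflicts with both the outcome definitions and the basis of the sample size.

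The adjustment rule adds a second open choice. Whether an adjusted estimate exists at all depends on someone judging that the arms differ at baseline. Each primary outcome is measured at T0 in every patient, so nothing prevents adjusting for it in all cases.

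**Working it through.** **Inputs from the Power section.** Mean school absence under usual care 40%; reduction of 15%; two-sided alpha 0.05; power 90%; 60 per group. No SD is given, and the text does not say whether the 15% is absolute or relative. I read it as 15 percentage points. A relative 15% would be 6 points, and 60 per group would then imply an SD of about 10.

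**1. The plan's figure as a comparison of means.** n per group = 2 × (1.960 + 1.282)² × SD² / 15². Setting n = 60 and solving for SD:

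SD = 15 / (3.242 × √(2/60)) = 25.3, a standardised difference of 15 / 25.3 = 0.59.

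So 60 per group is coherent if the SD is about 25. As the SD is not stated, the figure can be neither confirmed nor refuted: SD 20 would need 38 per group, SD 30 would need 85 and SD 35 would need 115.

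**2. The same figure as a comparison of proportions, 40% v 25%.** The pooled proportion is 0.325.

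Power = Φ[(0.15 × √60 − 1.960 × √(2 × 0.325 × 0.675)) / √(0.40 × 0.60 + 0.25 × 0.75)] = Φ[(1.162 − 1.298) / 0.654] = Φ(−0.21) = 0.42.

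For 90% power, n = [(1.298 + 1.282 × 0.654) / 0.15]², which is 203 per group. With a relative 15% (40% v 34%) it is 1,359 per group. The stated 60 does not come from proportions.

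**3. What a split would do if absence were normal.** Assume means 40 and 25, SD 25.3 and 60 per group. Success means absence at or below the cut-off. The success proportions are Φ((cut-off − 40)/25.3) and Φ((cut-off − 25)/25.3), put into the power formula of step 2.

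| Cut-off (absence) | Usual care | FITNET | Power |
|---|---|---|---|
| 15% | 0.162 | 0.347 | 65% |
| 25% | 0.277 | 0.500 | 71% |
| 32.5% | 0.384 | 0.616 | 73% |
| 40% | 0.500 | 0.723 | 71% |
| 50% | 0.653 | 0.838 | 65% |

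Against 90% for the means, the best split leaves 73%. A stricter cut-off of 10% leaves 59%.

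**4. The same question with bounded data.** The normal model puts Φ(−25/25.3) = 16% of the FITNET arm below zero absence, which cannot happen. As an alternative assumption, let near-full attenders have absence uniform on 0 to 10% (mean 5) and the rest uniform on 20 to 80% (mean 50). Means of 40 and 25 require near-full attenders to be (50 − 40)/45 = 22% and (50 − 25)/45 = 56% of the two arms. The SD is about 25. By simulation with 60 per arm, the t-test has about 90% power and a split at 10% absence about 97%. If the rest are uniform on 10 to 100%, the two figures are about 75% and 92%. Here the split gains power.

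**5. Scale of adjusted and unadjusted results.** At the 15% cut-off in step 3, the relative risk is 0.347/0.162 = 2.14, while the odds ratio from the unrounded proportions is 2.74. The same data give different figures on the two scales, before any adjustment.

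**The case against.** The strongest reply is that the phrase on appropriateness simply means by type of data. Linear regression is named for continuous measures, so the primary outcomes would get means and linear models, and relative risks would serve any binary outcome. A cut-off for recovery may well be in a full protocol or analysis plan that is not shown. This is a fair reading, and the missing cut-off alone would not be a finding. It does not remove the conflict, because the sentence is expressly about the primary outcome measures and none of them is binary.

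Several stronger inferences are tempting, and the article does not support them:

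- *Continuous outcomes would be adjusted by logistic regression.* The text reserves logistic regression for binary data.
- *The entry thresholds would serve as success criteria, so that some patients start as successes.* The article gives those thresholds for eligibility only and nowhere proposes them as outcome cut-offs.
- *The continuous route yields no between-arm effect with an interval.* The sentence is about differences between groups, and the linear regression named for adjustment yields a difference with its interval.
- *Odds ratios would be set against relative risks.* The article never mentions odds ratios, and a logistic model can be made to give adjusted relative risks. Step 5 shows only why the scale should be stated.
- *Dichotomising is certain to cost power.* Step 4 shows that it need not. The article itself says that most patients with a low activity pattern do not attend school at all, so a normal shape for absence is doubtful.
- *The scale will be picked after the data are seen.* The article does not say this; it only fails to rule it out.

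**Conclusion.** The point stands as a conflict within the article. The outcomes are continuous and the sample size rests on a mean, yet the stated effect measure may be a relative risk for which no binary endpoint exists. The firmest figure is that 60 per group gives 90% power as a comparison of means and about 42% as 40% v 25%. The first half rests on reading the 15% as percentage points and on a back-solved SD of about 25; the second needs no SD. The 65% to 73% range for a split outcome holds only under normality and for the tabulated cut-offs. It illustrates what is at risk and is not an established loss. Leaving adjustment to depend on an observed imbalance is a weakness in its own right: it makes the reported estimate depend on a judgement about the data, and it forgoes any precision that the T0 values would bring. This should be corrected, but it does not undermine the design.

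**What to change.** State that the main result for each primary outcome is the between-arm difference in means at T1 with a 95% confidence interval, from linear regression with the T0 value of that outcome as a covariate in every case, whether or not an imbalance is seen. Make any responder or recovery comparison secondary, with its definition and cut-off written down before database lock. Report adjusted and unadjusted results on the same effect scale; if relative risks are used, obtain the adjusted ones by modified Poisson regression with robust standard errors or by standardisation.

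The cost is a change of analysis wording. No new data are needed, since Table 2 already schedules all three outcomes at T0 and T1. The drawback is that the relative risk, which clinicians read easily, moves to a secondary place.

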### Randomization and blinding

Concealed randomisation will be performed by the data-management section of the Julius Centre for Health Sciences and Primary Care Utrecht. This randomization is computer-generated by creating 'blocks' with a size of 6, ensuring that the same number of participants will be allocated to each group. The investigators who are responsible for the inclusion will be blinded. Primary outcome parameters will be assessed by computer.

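### The main 6-month comparison is unadjusted, with adjustment added only if the arms differ at baseline, so the plan gives up precision that routine adjustment for the T0 value would provide

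*Protocol article*

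**What the plan says.** All of the analysis text is in the protocol article, Statistical Analysis.

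- The main efficacy analysis concerns the 6-month data. Group differences are "expressed as relative risks and 95% confidence intervals or as central estimators and variance measures where appropriate". No covariate enters at this step.
- Baseline data are first used as a check on the allocation: "Prognostically important baseline characteristics will be tabulated by treatment modality in order to evaluate success of randomisation".
- Adjustment follows only if that check shows something: "In case of baseline differences in prognosis between groups, treatment effects in primary outcome will additionally be adjusted for these differences". The models named for it are a logistic one if the outcome is binary and a linear one if it is continuous.

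Two other sections matter. Outcomes (Table 2) marks all three primary outcomes at T0 as well as at T1, and defines each as a score or a percentage. Randomization and blinding describes concealed, computer-generated allocation by "creating 'blocks' with a size of 6, ensuring that the same number of participants will be allocated to each group". It mentions no stratification by baseline severity.

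**The concern.** With concealed random allocation, any baseline difference between the arms is due to chance. Tabulating it cannot show whether adjustment is worthwhile. A covariate helps because it predicts the outcome, and it does so whether or not the arms happen to differ on it. The T0 value of the same measure is the obvious candidate, but the main comparison does not use it.

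Two things are at stake. The first is precision: wider confidence intervals and less power than the same patients could give. The second is clarity: observed imbalance decides whether readers see an adjusted estimate and what it is adjusted for, so the adjusted result is not fully fixed before the data are seen.

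**Working it through.** **The plan's own figure.** Power assumes that under usual care "the estimated average percentages of school absence, our primary endpoint, at the end of follow-up, will be 40" per cent. It then takes a 15% reduction, two-sided alpha 0.05 and 90% power, and arrives at 60 per group. No SD is stated, so 60 cannot be derived from these inputs alone. Reading the 15% as 15 percentage points and solving backwards:

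SD = 15 / [(1.96 + 1.2816) × √(2/60)] = 15 / (3.2415 × 0.1826) ≈ 25.3 points.

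This SD is implied by the calculation, not stated. It is needed only for interval widths in points. The power gain below starts from the stated 90% and does not depend on it.

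**Gain from planned adjustment.** Let r be the correlation between the T0 and T1 values. The article does not give r, so 0.3 to 0.7 is an assumed range. Linear regression on treatment and the T0 value multiplies the variance of the treatment effect by 1 − r².

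- Power = Φ(3.2415 / √(1 − r²) − 1.96)
- Equivalent gain in patients = 1 / (1 − r²) − 1
- Half-width of the 95% CI = 1.96 × 25.3 × √(1 − r²) × √(2/60)

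| r | Variance reduction | Equivalent extra patients | Power at 60 per group | Per group for 90% power | 95% CI half-width (points) |
|---|---|---|---|---|---|
| unadjusted | 0% | 0% | 90.0% | 60 | 9.07 |
| 0.3 | 9% | 10% | 92.5% | 55 | 8.65 |
| 0.5 | 25% | 33% | 96.3% | 45 | 7.85 |
| 0.7 | 49% | 96% | 99.5% | 31 | 6.48 |

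**Does the conditional rule recover this gain?** As written, the adjusted estimate is only additional, so the main comparison gains nothing. A more generous version lets the adjusted result replace the unadjusted one whenever the arms differ. This was simulated with 20,000 trials per setting, 60 per arm and SD 25.3. The article gives no criterion for imbalance, so a T0 difference with p < 0.05 was assumed.

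| Power under a 15-point effect | r = 0.3 | r = 0.5 | r = 0.7 |
|---|---|---|---|
| Unadjusted | 89.5% | 89.7% | 89.7% |
| Adjusted only if imbalanced | 89.8% | 90.5% | 91.3% |
| Planned adjustment | 91.9% | 96.0% | 99.5% |

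Even this version captures little of the gain. At r = 0.5 it gains 0.8 of the 6.3 available points.

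**Type I error in the same simulation (r = 0.3 / 0.5 / 0.7).**

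- Unadjusted: 5.0 / 5.1 / 4.9%.
- Adjusted result used only if imbalanced: 4.8 / 4.5 / 3.6%.
- Either result counted when imbalanced: 5.1 / 5.2 / 5.1%.
- Better of the two picked in every trial: 6.6 / 7.3 / 8.4%. The plan does not permit this.

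**The case against.** The best defence is that nothing here is invalid. The unadjusted comparison is always reported, is unbiased under randomisation, and is not replaced by the adjusted one. That stands. The missing imbalance threshold and covariate list are details that an article may leave to a fuller document, and they are not held against it. The conditional rule itself is stated in the article, and a threshold supplied later would not remove it.

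The size of the gain is also open to challenge. One correlation range is applied to three different measures. Entry requires fatigue of at least 40 on a scale from 8 to 56, which narrows the baseline range and may lower r for that outcome. At r = 0.3 the power gain is only about 2 points. This stands too: 49% is the favourable end of an assumed range.

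A reader might infer several stronger points that the article does not support.

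- *The trial's reported effect is chosen from the data, or alpha is inflated.* The simulation puts type I error at no more than about 5.2% under the rule as written.
- *The choice is made after unblinding.* The trigger is a baseline table by arm. The text does not say that outcomes are known when it is read.
- *A chance baseline difference leaves the result uncorrected.* A visible prognostic difference is exactly the case in which the plan adds an adjusted estimate.
- *Relative risks will be set against odds ratios.* Table 2 defines no binary primary outcome, and naming logistic regression does not commit the authors to reporting an odds ratio. At most this calls for a clarification.

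Finally, school presence is a bounded percentage, and Appendix 1 says that most patients with a low activity pattern are not at school at all. A plain linear model with model-based standard errors may fit it poorly. That affects how the adjusted analysis is fitted, not whether to plan one.

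**Conclusion.** The point holds as an efficiency improvement to a valid analysis. The plan collects the T0 value of every primary outcome, leaves it out of the main comparison, and lets observed imbalance decide whether an adjusted estimate is shown and with what in it. For an assumed T0-T1 correlation of 0.3 to 0.7, planned adjustment would reduce the variance by 9% to 49% and move the stated 90% power to about 92% to 99%. The documents cannot narrow that range, and fatigue may sit near its lower end. The interval widths rest further on the back-solved SD of 25.3 points. The finding does not extend to bias, to a material alpha problem, or to the adequacy of the sample size; the missing SD is a separate matter.

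**What to change.** Replace the conditional sentence in Statistical Analysis with a fixed rule:

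- For each continuous primary outcome, the main analysis is the T1 difference between groups with its 95% CI, from linear regression on treatment and the T0 value of the same outcome, fitted whatever the baseline table shows.
- For school presence, use robust or bootstrap standard errors if its bounded distribution requires them.
- Any further covariates are named in advance. The unadjusted difference is reported as supportive.
- If a binary summary is reported, adjusted and unadjusted results are both given as relative risks, for example by modified Poisson regression or by marginal standardisation from the logistic model.

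The baseline table can stay as a description of the sample. The cost is a few sentences. The T0 data are already scheduled, and linear regression is already the method named for continuous outcomes.
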